## Abstract

**Background:**

Patients with breast cancer undergo various treatments according to their tumor subtype and cancer stages within 1 year after being diagnosed. Each treatment may cause treatment-related symptoms that have negative impacts on patients’ health and quality of life (QoL) The symptoms can be mitigated when exercise interventions are appropriately applied to patients’ physical and mental conditions. Although many exercise programs were developed and implemented during this period, the effects of tailored exercise programs according to symptoms and cancer trajectories on patients’ long-term health outcomes have not yet been fully elucidated. Therefore, this randomized controlled trial (RCT) aims to investigate the effect of tailored home-based exercise programs on short-term and long-term physiological outcomes in patients with breast cancer.

**Methods:**

This 12-month RCT includes 96 patients with (stages 1–3) breast cancer randomly assigned to the exercise or control groups. Participants in the exercise group will receive an exercise program tailored to their phase of treatment, type of surgery, and physical function. During post-operative recovery, exercise interventions will be emphasized to improve shoulder range of motion (ROM) and strength. During chemoradiation therapy, exercise intervention will focus on improving physical function and preventing loss of muscle mass. Once chemoradiation therapy is completed, exercise intervention will focus on improving cardiopulmonary fitness and insulin resistance. All interventions will be home-based exercise programs supplemented with once-monthly exercise education and counseling sessions. The main outcome of the study is fasting insulin level at baseline, 6 months, and 1 year post-intervention. Our secondary outcomes include shoulder ROM and strength at 1 month and 3 months, body composition, inflammatory markers, microbiome, QoL, and physical activity levels at 1 month, 6 months, and 1 year post-intervention.

**Conclusion:**

This trial is the first tailored home-based exercise oncology trial to better understand the comprehensive phase-dependent short- and long-term effects of exercise on shoulder function, body composition, fasting insulin, biomarkers, and microbiome. The results of this study will inform the development of effective exercise programs tailored to the needs of patients with breast cancer post-operatively.

**Trial registration:**

The protocol for this study is registered with the Korean Clinical Trials Registry (KCT0007853).

**Supplementary Information:**

The online version contains supplementary material available at 10.1186/s12885-023-10664-1.

## Background

Globally, breast cancer is the most commonly diagnosed cancer (cancer incidence, 24.2%; and cancer mortality, 15.0%) among women [1], and 0.68 million women die from breast cancer in 2020 [1]. In Korea, the incidence of breast cancer has been increasing steadily, with 25,452 new cases, and it was the most common cancer among women in 2020 (24.7% of all cancer cases in women) [2]. Most patients with breast cancer undergo surgical resection and sampling or removal of axillary lymph nodes, followed by post-operative therapy [3]. Despite advances in surgical and therapeutic techniques, breast cancer surgery still results in various post-operative morbidities and complications.

The most frequently reported post-surgical complications are reduced shoulder range of motion (ROM), reduced shoulder strength, chronic pain, and sensory disturbances [4]. Patients also experience arthralgia, cellulitis, rotator cuff disease, shoulder impairment [5], axillary web syndrome [6], postural problems, or bothersome scarring [7] 1 month post-surgery. Lymphedema, the most invalidating post-surgical problem [8], can last for years after surgery. Furthermore, breast cancer surgery leads to greater psychological morbidity and poorer quality of life (QoL) in breast cancer survivors [6]. Although the impact of post-operative morbidities and complications on physical and psychological problems remains for a short time [9], upper limb dysfunction, such as decreased shoulder ROM and strength and pain tend to continue in the year after surgery [10]. In addition, gut microbiome has been shown to be associated with obesity [11], cellular dysplasia, and malignancies including breast cancer [12]. Dysbiosis could include disruption of bacterial homeostasis, which may influence breast tumorigenesis and potentially increase breast cancer risk [13]. Therefore, the clinical management of breast cancer requires a holistic multidisciplinary approach.

Approximately 1 month after surgery, most patients with breast cancer undergo chemoradiation therapy, which lasts for approximately 6 months. During this period, patients experience various treatment-related symptoms, such as nausea, vomiting, fatigue, and anorexia [9]. Since patients still do not fully recover from surgery, the additional burden of chemo-radiation treatment affects patients’ physical and psychological health. As a result, most patients with breast cancer experience side effects, such as loss of muscle mass, increased adiposity, and decreased physical fitness [14]. Furthermore, various breast cancer treatments have a negative impact on mental health, which can lead to mood problems, such as fear, anger, uncertainty about the future, depression, and anxiety [15–17]. Moreover, during the recovery period of 6–12 months after surgery, a variety of treatments for breast cancer using chemotherapy can induce metabolic changes, including decreased lean body mass and muscle strength, and a subsequent increase in body weight [18] and insulin resistance [19], which in turn may be associated with increased mortality among patients with breast cancer [17, 19].

Several studies have shown that exercise interventions can be an effective self-management strategy. Exercise has beneficial effects on fasting insulin levels [20], fatigue [21], body composition [22], and cardiovascular function [23] in patients with breast cancer [24, 25]. Furthermore, positive effects of exercise on the symptoms and prognosis of patients with breast cancer may have been mediated by changes in the microbiome [26]. Although many exercise programs have been developed and implemented, different types of breast cancer surgeries may cause damage to different muscles and fasciae, which would influence certain movements of the shoulder joints [27, 28]. Furthermore, each time point (1 month, 6 months, and 12 months) after surgery may require a different approach because the prevailing symptoms are likely to differ at different phases of post-operative recovery [28–30]. Furthermore, the ideal timing and types of exercise for patients with breast cancer experiencing various physical dysfunctions and symptoms have not yet been fully studied.

Therefore, the purpose of the current study is to evaluate the short- and long-term effects of a tailored exercise program according to the phase of treatment and the patient’s condition on fasting insulin levels, body composition, shoulder function, QOL, patient-reported outcomes, and the microbiome in patients with breast cancer for up to 12 months.

## Study objectives

### Objectives

#### Primary objective

To evaluate the effect of the exercise program on changes in fasting insulin levels after exercise intervention (after chemotherapy, 12 months after surgery).

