#### Exploratory objective

To investigate changes in insulin levels, body composition, shoulder function, QOL, patient-reported outcomes, and the diversity and composition of the gut microbiome of patients with breast cancer from the day before surgery to 12 months after surgery.

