## Methods

### Study design

A randomized, controlled, parallel-group pre-test and repeated post-test design will be applied to investigate the effect of the tailored exercise program for patients with breast cancer at each time point after surgery (post-operative day 1, third outpatient visit; 1 month from the baseline; during chemotherapy, fourth outpatient visit; 6 months from the baseline; during and after chemotherapy, and fifth outpatient visit; 12 months from the baseline; after chemotherapy). The exercise intervention and evaluation schedule can be changed based on the individual treatment period of chemotherapy (Table 1). The feasibility of the intervention and exploratory analysis of the effects of exercise on breast cancer patients were tested in a pilot study (KCT0006997). The results of the pilot study have been used to optimize the current study design by integrating videos for exercise sessions at home. This study will recruit participants from Severance Hospital, Yonsei University Health System, Seoul, Korea.

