### Eligibility criteria

#### Inclusion criteria

Eligibility criteria will include the following: [1] women aged 19–70 years; [2] patients with histologically confirmed stage I, II, and III breast cancer; [3] medically suitable for evaluation and participation in exercise intervention; [4] no evidence of distant metastasis or locally recurrent breast cancer; and [5] ability to understand and provide written informed consent in the Korean language.

**Table 1 Tab1:** Flow diagram for the schedule of enrollment, interventions, and assessments

TIME POINT	VISIT 1	VISIT 2 *[Phase 1]*	VISIT 3 *[Phase 1]*	VISIT 4 *[Phase 2]*	VISIT 5 *[Phase 3]*
	Baseline, (Before surgery)	POD 1	1 month from the baseline (± 2 weeks)	6 months from the baseline (± 1 month)	12 months from the baseline (± 1 month)

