## Randomization

Eligible participants will be randomly assigned to the exercise or control group, considering age, surgery method, and neoadjuvant chemotherapy as potential confounders. Each group would be matched into pairs such that the average age, surgical method, and neoadjuvant chemotherapy percentage are approximately equal (1:1 ratio). The exercise group will be provided with a systematic exercise program from post-operative day (POD) 1 to 12 months after surgery. The control group will receive the same preoperative and post-operative medical care and treatment as the exercise group (i.e., the usual care group thereafter), except for post-operative exercise. To evaluate the effects of the exercise intervention, measurements will be conducted five times for all the participants. The registration number of the Korean Clinical Trials Registry is KCT0007853. Data will be de-identified for analysis, and only study leaders at the university hospital will have access to identifiable information for all participants.

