#### Statistical analysis methods

All analyses will be performed using the SPSS version 26.0 software (IBM Corp., Armonk, NY, USA). A Chi-square test for categorical variables and an independent t-test for continuous variables will be used to test group differences at baseline. Two-way repeated-measures ANOVAs will be conducted to observe the effects of the intervention on fasting insulin levels, shoulder ROM and function, body composition, inflammatory markers, microbiome, QOL, and physical activity levels. Paired t-tests will be performed to examine the difference between outcome measurements and baseline values, while independent t-tests will be employed to examine group differences in variables at each time point. The Bonferroni correction method will be used to correct for multiple tests. Analysis of covariance (ANCOVA) will be applied to test the effect of an exercise intervention on body composition, PA, and complications, since these variables will be measured after adjusting for baseline values. First, from baseline to 1 month from the baseline will be calculated and then the differences between groups will be examined after adjusting for baseline values and surgical methods. The same methods will be used for 6 and 12 months.

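### Neoadjuvant chemotherapy and age are balanced at allocation but left out of the stated analyses, which costs precision and blurs the within-arm changes

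*Protocol article*

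**What the plan says.** All references are to the protocol article.

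- **Primary objective:** the effect of exercise on "changes in fasting insulin levels after exercise intervention (after chemotherapy, 12 months after surgery"). Study design labels the last visit in the same way: "12 months from the baseline; after chemotherapy".
- **Baseline:** Table 1 heads the first visit "Baseline, (Before surgery"), and the exploratory objective follows patients "from the day before surgery to 12 months after surgery". This applies to every participant.
- **Randomization:** patients are allocated "considering age, surgery method, and neoadjuvant chemotherapy as potential confounders", with the two arms to be made roughly equal on all three at a 1:1 ratio. Neoadjuvant patients are therefore expected, and the eligibility criteria do not exclude them.
- **Statistical analysis methods:** fasting insulin gets a two-way repeated-measures ANOVA, paired t-tests against baseline and independent t-tests at each time point. No covariate is named. ANCOVA is assigned to body composition, physical activity and complications, where "the differences between groups will be examined after adjusting for baseline values and surgical methods". Neoadjuvant chemotherapy and age appear in no stated model.
- **Background:** "Approximately 1 month after surgery, most patients with breast cancer undergo chemoradiation therapy", and "a variety of treatments for breast cancer using chemotherapy can induce metabolic changes", among them loss of lean mass, weight gain and insulin resistance.

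**The concern.** Two sections do not match. Randomization treats three variables as important enough to balance. The analysis section carries one of them (surgical method) into the ANCOVAs and none into the insulin analysis.

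Neoadjuvant chemotherapy matters most here because it determines what the baseline means. In a neoadjuvant patient the pre-surgery sample is taken after pre-operative chemotherapy. In a patient who has adjuvant chemotherapy, the change from baseline spans that treatment. In a patient who has none, it does neither. Since the Background links chemotherapy to insulin resistance, the protocol's own reasoning makes the factor a plausible predictor of the insulin change.

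Two things are at stake. First, when arms are balanced on a prognostic factor and the analysis ignores it, the variation between strata goes into the error term although allocation has already removed it from the contrast. The calculated standard error is then too large. Second, the paired t-tests and the exploratory time course average over patients with different courses, so their size depends on the mix recruited.

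**Working it through.** **Inputs.** The article gives neither the neoadjuvant share *p* nor the difference *d* in mean 12-month insulin change between neoadjuvant and other patients (in within-stratum SDs). Both are assumed: *p* = 0.2–0.4 and *d* = 0.5–1.0, with *d* = 0.25 as a low case. The plan has no figure of its own on this point to reproduce. From Sample size, only the 80 evaluable patients are used, as 40 per arm.

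**Step 1: bias.** With *k* more neoadjuvant patients in one arm of 40, the contrast shifts by *d* × *k*/40. With exact balance, *k* = 0 and the shift is 0. With *k* = 4, it is 0.5 × 4/40 = 0.05 SD to 1.0 × 4/40 = 0.10 SD. Planned balance therefore removes the bias, and a small residual imbalance leaves a small one.

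**Step 2: standard error.** If the factor is ignored, the estimated variance of the change is multiplied by V = 1 + *p*(1−*p*)*d*², and the standard error by √V.

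**Step 3: test behaviour under exact balance.** The true sampling variance of the contrast stays at its within-stratum value, so the test in effect uses a critical value of 1.96√V. In the normal approximation, the type I error is 2[1 − Φ(1.96√V)]. For an effect that the adjusted test detects with 80% power (1.96 + 0.84 = 2.80 standard errors), the power is Φ(2.80 − 1.96√V).

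| *p* | *d* | V | √V | 1.96√V | Type I error | Power |
|---|---|---|---|---|---|---|
| 0.4 | 0.25 | 1 + 0.24 × 0.0625 = 1.015 | 1.007 | 1.975 | 4.8% | 79.6% |
| 0.2 | 0.5 | 1 + 0.16 × 0.25 = 1.04 | 1.020 | 1.999 | 4.6% | 78.9% |
| 0.3 | 0.5 | 1 + 0.21 × 0.25 = 1.0525 | 1.026 | 2.011 | 4.4% | 78.6% |
| 0.3 | 1.0 | 1 + 0.21 × 1 = 1.21 | 1.100 | 2.156 | 3.1% | 74.1% |
| 0.4 | 1.0 | 1 + 0.24 × 1 = 1.24 | 1.114 | 2.183 | 2.9% | 73.2% |

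Over the assumed range the standard error is about 2% to 11% too large. If the factor were not balanced, so that its variation did enter the contrast, power would be Φ(2.80/√V − 1.96): 78.4% at *p* = 0.2, *d* = 0.5 and 71.1% at *p* = 0.4, *d* = 1.0.

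**Step 4: within-arm change.** Relative to the other patients' mean, the pooled change in an arm moves by *p* × *d*: from 0.2 × 0.5 = 0.10 SD to 0.4 × 1.0 = 0.40 SD. This shift is common to both arms and cancels in the contrast. It remains in the paired t-tests and in the exploratory description.

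**The case against.** Several counter-arguments are sound.

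- **Validity.** A reader might infer that mixing patients with different courses invalidates the primary result. The documents do not support this. Randomization makes the neoadjuvant percentage approximately equal between arms, and the resulting test errs on the conservative side.
- **Recovery.** A reader might also infer that the change in neoadjuvant patients is mainly recovery from a disturbed baseline. The Background passage on metabolic change concerns the 6–12 months after surgery. It does not say how large the effect of pre-operative chemotherapy on insulin is, or how fast it reverses. The point needs only that the changes may differ.
- **One course for all.** It is tempting to say that the design assumes surgery followed by chemotherapy throughout. Study design lets the schedule follow the individual chemotherapy period, and Exercise program sets the phases by individual treatment. Neither provision moves the pre-surgery baseline, but both rule out that broad claim.
- **Time point.** Primary outcome measures fixes the outcome at 12 months (± 1 month) with no chemotherapy condition. The parenthesis in the primary objective is then an imprecise label, inaccurate only for patients who have no chemotherapy. It is not a second definition.
- **Size.** At *d* = 0.25 almost nothing is lost, and no passage supports a difference as large as 1.0 SD.
- **Left to the analysis plan.** Covariates for the insulin model may stand in a plan that is not shown. This weakens the point for insulin. It does not remove the mismatch in the ANCOVA list, which the article does fix and which keeps one allocation factor out of three.

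**Conclusion.** The point holds as a matter of efficiency and interpretation, not of bias. Two allocation factors, neoadjuvant chemotherapy and age, are missing from every stated model, and surgery method is missing from the insulin analysis. Neoadjuvant chemotherapy is the one whose omission can be argued from the protocol's own rationale, because it decides whether baseline comes before or after chemotherapy.

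If 20–40% of patients are neoadjuvant and the mean change differs by 0.5–1.0 SD, the primary standard error is about 2% to 11% too large. Under exact balance, power that would be 80% with adjustment falls to between 78.9% and 73.2%. These figures rest wholly on the assumed share and difference, and on balance being achieved. Pooled within-arm changes would move by 0.10 to 0.40 SD with case mix under the same assumptions and should not be read as the course of any one group. The wording of the primary time point is a minor matter.

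**What to change.** 1. **Insulin:** in the 12-month comparison, adjust for baseline insulin and the three allocation factors: neoadjuvant chemotherapy (yes/no), surgery method and age. If the repeated-measures form is kept, let the factors interact with time.
2. **ANCOVAs:** add neoadjuvant chemotherapy and age to baseline value and surgical method.
3. **Minor, description:** show the within-arm insulin course by chemotherapy timing in three groups (neoadjuvant, adjuvant, none). A neoadjuvant yes/no split would still pool patients given adjuvant chemotherapy with those given none.
4. **Minor, wording:** state the time point in the primary objective as 12 months from baseline, as in Primary outcome measures, regardless of chemotherapy received.

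**Cost.** No extra patients are needed, and the allocation factors are already recorded. The three-group description needs a record of post-operative chemotherapy, which the individual scheduling already presupposes. The 12-month model uses four degrees of freedom beyond the arm effect if surgery method has two categories and age enters linearly. In a repeated-measures model with three insulin visits, each binary factor takes one degree of freedom for its main effect and two for its interaction with time. With about 80 evaluable patients, either is affordable. The covariates should be fixed before the outcome data are seen.

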#### Secondary objective

To evaluate the effect of the exercise program on changes in shoulder function, body composition, QOL, patient-reported outcomes, and the diversity and composition of the gut microbiome after an exercise intervention.

#### Exploratory objective

To investigate changes in insulin levels, body composition, shoulder function, QOL, patient-reported outcomes, and the diversity and composition of the gut microbiome of patients with breast cancer from the day before surgery to 12 months after surgery.

## Methods

### Study design

A randomized, controlled, parallel-group pre-test and repeated post-test design will be applied to investigate the effect of the tailored exercise program for patients with breast cancer at each time point after surgery (post-operative day 1, third outpatient visit; 1 month from the baseline; during chemotherapy, fourth outpatient visit; 6 months from the baseline; during and after chemotherapy, and fifth outpatient visit; 12 months from the baseline; after chemotherapy). The exercise intervention and evaluation schedule can be changed based on the individual treatment period of chemotherapy (Table 1). The feasibility of the intervention and exploratory analysis of the effects of exercise on breast cancer patients were tested in a pilot study (KCT0006997). The results of the pilot study have been used to optimize the current study design by integrating videos for exercise sessions at home. This study will recruit participants from Severance Hospital, Yonsei University Health System, Seoul, Korea.

### Eligibility criteria

#### Inclusion criteria

Eligibility criteria will include the following: [1] women aged 19–70 years; [2] patients with histologically confirmed stage I, II, and III breast cancer; [3] medically suitable for evaluation and participation in exercise intervention; [4] no evidence of distant metastasis or locally recurrent breast cancer; and [5] ability to understand and provide written informed consent in the Korean language.

**Table 1 Tab1:** Flow diagram for the schedule of enrollment, interventions, and assessments

TIME POINT	VISIT 1	VISIT 2 *[Phase 1]*	VISIT 3 *[Phase 1]*	VISIT 4 *[Phase 2]*	VISIT 5 *[Phase 3]*
	Baseline, (Before surgery)	POD 1	1 month from the baseline (± 2 weeks)	6 months from the baseline (± 1 month)	12 months from the baseline (± 1 month)
**ENROLLEMENT**					
Informed consent	○				
Sociodemographic information	○	○	○	○	○
**INTERVENTIONS**					
Exercise group		○	○	○	○
Usual care group					
**ASSESSMENTS**					
Body composition	○		○	○	○
Shoulder ROM & Strength	○		○	○	○
Physical activity	○		○	○	○
SPADI	○		○	○	○
Serum markers	○			○	○
Microbiome analysis	○			○	○
Nutritional status	○			○	○
QOL	○		○	○	○

Notes. POD, post-operative day; ROM: Range of motion; SPADI: Shoulder pain and disability index; QOL: Quality of life

